**Figure 2 figure2:**
[figure not shown]
Example of a high-intensity interval training session and the high and low intensities performed.

Exercise intensity is gradually increased within the first 4 weeks of the intervention, whereby the participants begin the high-intensity interval bouts at 60% POmax, increase by 10% each week until 90% is reached, and then maintain at 90% for the remainder of the intervention (Figure 3). If a participant is unable to achieve compliance with the prescribed HIIT program, a moderate-intensity interval training (MIIT) program is substituted as an alternative exercise prescription. A single session is considered noncompliant if the number of high-intensity bouts achieving the target power output is <80% (eg, if ≥3 high-intensity bouts do not reach the prescribed power output). If 3 concurrent exercise sessions are reported as noncompliant, the participant is offered the MIIT program instead. Within the MIIT program, participants continue to complete intervals at a 1 minute:1 minute (work:recovery) ratio; however, the high-intensity bout is replaced with a moderate-intensity power output target. The intensity of the moderate interval is calculated as a percentage of the individual’s estimated VO_2max_ and will be selected according to the highest intensity that the participant may tolerate or complete. After the aerobic exercise session, the participants will perform 1 set of 3 to 4 static stretching exercises held for 30 seconds.

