### Sample Size Calculation

We will enroll 50 patients with breast cancer (n=25, 50% per group) in this study. We estimate that the dropout rate will at most be 20%. Assuming a 20% dropout, data from 40 (n=20, 50% per group) patients will be available for the analyses. With this sample size, we will be able to estimate within-group means for our outcome variables with a 95% CI of –0.47 to +0.47 SD units and mean differences between groups with a 95% CI of –0.64 to +0.64 SD units. Although the primary objective of the analysis for this pilot study is not to detect a between-group difference but to estimate the effect size for designing a subsequent confirmatory study, we also calculated a detectable effect size for the between-group comparison for reference. This sample size offers 80% power to detect a between-group difference at a .05 2-sided *α* level when the difference is 0.91 SD units.

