### Statistical Analysis

Analyses will reflect the trial hypotheses that involve comparisons of HIIT and AC. Initial descriptive analyses will evaluate baseline comparability between the 2 intervention groups using the 2-sample, 2-tailed *t* test or 2-sample Wilcoxon test for continuous variables and the chi-square test or Fisher exact test for categorical variables. The primary analysis variables will be changed from baseline to week 16 of neuroimaging and cognitive function measures. Summary statistics (mean, SD, median, IQR, minimum, and maximum) will be used to describe the distribution of the variables. The mean and median will be reported along with the corresponding 95% CIs. Paired tests will be performed for these continuous outcomes for each group to assess whether there is a significant difference between baseline and week 16 in each group. For between-group comparison, a 2-sample *t* test will be performed. Analysis of covariance will also be used to assess the intervention effect on those continuous outcomes (changes from baseline to week 16), adjusting for patient baseline characteristics and other clinical covariates, including any participant who is required to switch to MIIT. Furthermore, those who are transferred to the MIIT group will be included in the HIIT group in the primary analysis based on the intention-to-treat principle. As an exploratory analysis, we will identify baseline factors of the patients who are likely to be transferred to the MIIT group. We will then exclude those who are transferred to the MIIT group and compare the HIIT and AC groups adjusting for factors that affect the transfer from HIIT to MIIT. Chi-square tests will be used for group comparison of binary outcomes (eg, the occurrence of adverse events). The magnitude of the intervention effect on binary outcomes will be summarized using odds ratio and the corresponding 95% CI. For each analysis, a 2-sided *P* value of <.05 will be considered statistically significant. As this is a pilot study, we will not adjust for multiple testing. Linear mixed-effects models will be used to estimate the trajectories of those repeatedly measured continuous outcomes across the intervention to assess group differences and explore the impact of potential prognostic factors (eg, body weight, age, fat mass, race, and menopausal status) on outcomes. Linear mixed-effects models will also be used for exploratory analysis of potential neuroimaging biomarkers. The primary analysis will include all completed outcome assessments (regardless of whether the woman stayed on the intervention), inviting those who drop out of the intervention to return for outcome assessments. The only missing data would be of those who drop out of the intervention and do not return for outcome assessments. Preliminary analyses will compare women who do and do not contribute to this analysis of baseline characteristics. A sensitivity analysis will include multiple imputations of all missing outcome data, including those patients who have missing assessments.

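### The ANCOVA adjusts for switching to MIIT, which happens after randomization and only in the HIIT arm, so its treatment coefficient is not the intention-to-treat effect

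*Protocol article*

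**What the plan says.** Under Statistical Analysis, the protocol article compares the arms on change from baseline to week 16 with a two-sample t test. It adds an ANCOVA to assess the intervention effect on the same changes, "adjusting for patient baseline characteristics and other clinical covariates, including any participant who is required to switch to MIIT". The next sentence states that "those who are transferred to the MIIT group will be included in the HIIT group in the primary analysis based on the intention-to-treat principle". A later analysis that leaves switchers out, and adjusts for the factors behind the transfer, is labelled exploratory.

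The Intervention section defines the switch: "If 3 concurrent exercise sessions are reported as noncompliant, the participant is offered the MIIT program instead". A session counts as noncompliant when too few high-intensity bouts reach the target power. The AC Group section gives control participants home stretching for 16 weeks and offers them HIIT only afterwards.

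The Sample Size Calculation section says that the pilot's main purpose is to estimate an effect size for a later confirmatory trial.

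**The concern.** A covariate in a randomized comparison should not be a consequence of the assigned treatment. Switching to MIIT is one: it depends on how a woman performs in HIIT sessions after randomization. Up to week 16 it is also zero by design for everyone in AC. Women in AC who would have failed HIIT cannot be identified, so they stay in the control mean, while their counterparts in HIIT are taken out of the treatment contrast by the indicator. The comparison is then no longer between groups formed by randomization.

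The ANCOVA would be reported as an intervention effect, from a pilot whose purpose is to supply an effect size. A reader would reasonably take the coefficient as an intention-to-treat estimate, given the sentence that follows it.

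**Working it through.** **1. The plan's own figures.** The article enrols 50 and assumes 20% dropout: 50 × 0.8 = 40, or 20 per arm. 
- Between-group 95% CI half-width: t(0.975, 38) × √(2/20) = 2.024 × 0.316 = 0.640 SD (stated: 0.64). 
- Within-group half-width: 2.093/√20 = 0.468 SD (stated: 0.47). 
- Power of a two-sample t test at 0.91 SD with 20 per arm: 80.1% (stated: 80%). 

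These figures reproduce, describe an unadjusted two-sample comparison, and are not in dispute.

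**2. What the coefficient estimates.** Let T = 1 for HIIT, and S = 1 for a participant who switched to MIIT. S = 1 occurs only where T = 1, so the model Y = a + bT + cS fits three separate means: AC (a), HIIT non-switchers (a + b) and HIIT switchers (a + b + c). Hence

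b = mean(HIIT non-switchers) − mean(all AC).

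A numerical check with 20 per arm and 6 switchers gave b = −0.131 both from the regression and from the difference of those two means. The difference between the full arms in the same data was +0.018. Adding baseline covariates makes these adjusted means. Switchers then help to estimate the slopes and residual variance, but the contrast is still non-switchers against all AC.

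**3. Distance from the intention-to-treat effect.** Let p be the share who switch, or would switch if assigned HIIT (the same in both arms by randomization). Let d be the deficit in change of such women without treatment, τ the effect in non-switchers, and m the effect in switchers.
- Intention-to-treat effect = (1 − p)τ + pm
- Coefficient b = τ + pd
- Difference = p × [d + (τ − m)]

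The sign depends on d and on τ − m. The article gives neither of these, nor p.

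**4. Size with no true effect (τ = m = 0).** The difference is pd. Simulation with 20 per arm, 4,000 replicates, residual SD 1 and no baseline covariates:

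| Assumed p | Assumed d (SD) | p × d | Simulated coefficient | Type I error with the switch term |
|---|---|---|---|---|
| 20% | 0.5 | 0.10 | 0.10 | 5.6% |
| 30% | 0.5 | 0.15 | 0.15 | 6.3% |
| 30% | 0.8 | 0.24 | 0.24 | 9.1% |
| 40% | 0.8 | 0.32 | 0.32 | 13.0% |

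Without the switch term, the mean coefficient was within 0.01 SD of zero and type I error was about 5%.

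**5. The direction can reverse.** A second simulation let a continuous trait drive both switching and outcome, with correlation ρ.
- No true effect, ρ = 0: no bias.
- No true effect, ρ = −0.3 (switchers do better): −0.06 to −0.19 SD for 10% to 40% switching.
- True HIIT effect 0.5 SD, ρ = 0, 30% switching, MIIT effect 0.25 SD: coefficient 0.51 against intention-to-treat 0.43. The formula gives a gap of 0.3 × 0.25 = 0.075.
- The same with MIIT effect 0.8 SD: 0.51 against 0.60. The formula gives 0.3 × (−0.3) = −0.09.

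**The case against.** **An intention-to-treat contrast is already planned.** The t test keeps switchers in HIIT, and the primary analysis uses all completed assessments whether or not the woman stayed on the intervention. This stands, and it confines the fault to the ANCOVA. The intention-to-treat sentence concerns the primary analysis, and the article does not say that the ANCOVA is primary. The two sentences are therefore at odds in purpose rather than a strict contradiction.

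**A reader might infer that the ANCOVA is biased toward HIIT.** That is plausible if switchers carry a heavier treatment burden. But the power target is a percentage of each woman's own maximum, so missing it is not simply a sign of low fitness. The article states nothing about switchers' prognosis or the relative effect of MIIT, so the direction is not established.

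**A reader might also infer that a biased estimate will be carried into the confirmatory trial.** The article does not say which estimate supplies the effect size, so this is a risk and not a planned step.

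**The wording is loose.** The phrase names participants rather than a variable, and might mean only that switchers are included in the analysis. Since it stands in the list of things adjusted for, a switch covariate is the plain reading. If the other meaning was intended, the sentence still needs rewording.

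**The sizes are illustrative.** Baseline covariates would absorb whatever part of the deficit they predict. At a deficit of 0.5 SD the bias is 0.10 to 0.15 SD, small beside the stated half-width of 0.64 SD, and hypothesis testing is not the pilot's main aim. This is fair, but bias does not average out as sampling error does, and it enters a point estimate that may be used for planning.

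**Conclusion.** The point holds for the ANCOVA. As written, its treatment coefficient is a comparison of HIIT non-switchers with all AC participants, and not the intention-to-treat effect. That follows from the algebra and from the article's own description of the switch, whatever the switch rate.

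The size and direction of any bias rest on assumptions. With 20% to 40% switching, a deficit of 0.5 to 0.8 SD and no baseline covariates, it is about 0.10 to 0.32 SD toward HIIT, with type I error about 6% to 13%. The upper end is half of the stated half-width (0.32/0.64). If switchers have the better prognosis, or MIIT works better than HIIT, the bias runs the other way.

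The t test and the sample size figures are unaffected. The consequence would come from using the ANCOVA estimate for planning. As an assumed illustration, if the true effect is 0.50 SD and the estimate is 0.65 SD (0.50 + 0.15), a trial planned for 80% power would enrol 39 instead of 64 per arm and have about 59% power.

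**What to change.** In Statistical Analysis:
- Delete the MIIT-switch term from the ANCOVA and limit its covariates to variables measured before randomization.
- State that switchers are analysed as HIIT in the ANCOVA as well as in the t test.
- Keep the non-switcher comparison only in the exploratory analysis already planned, and label it as not protected by randomization.

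In the null simulations, the model without the switch term had a mean within about 0.015 SD of zero and type I error of 4.6% to 5.6%. The cost is about one sentence of text. Sample size, data collection and patient burden do not change.

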#### Covariates

##### Participant Characteristics

Participant demographic and medical history data are collected at baseline with the administration of a study-tailored questionnaire. In addition, patients complete the Socioeconomic Status Questionnaire to determine economic demographics, education level, and socioeconomic status [70]. Changes in demographic and medical history data (eg, medical conditions, medication, and cancer treatment) will be monitored throughout the study period and confirmed at each testing time point.

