### Intervention

#### HIIT Group

Participants randomized to this group partake in a clinic-based HIIT program using a cycle ergometer 3 days per week for 16 weeks under the supervision of a trained exercise oncology specialist. Before beginning the exercise session, participants undergo a screening procedure to ensure that they are fit to participate. Participants are permitted to participate in the exercise session if they present with normal body temperature (≤100 °F or ≤37.8 °C), resting HR (absence of bradycardia, <60 beats per minute; or tachycardia, >100 beats per minute), and resting blood pressure (≤200/120 mm Hg). In addition, participants complete the Exercise-Induced Feeling Inventory [72] before and after the HIIT session to assess the participants’ feeling state changes after exercise and self-motivation to adhere to an aerobic exercise regimen. Participants also complete the Therapy-Related Symptom Checklist [73], a 25-item questionnaire, to assess and identify patient-reported symptom occurrence and severity.

The cycle-based HIIT exercise session consists of a 5-minute warm-up period at 10% of POmax (watts; calculated from the cardiopulmonary exercise test) followed by a 20-minute stimulus period consisting of alternating high-intensity interval bouts at 90% POmax (based on individual fitness level) with a recovery bout at 10% at a 1 minute:1 minute (work:recovery) ratio (Figure 2). Following the stimulus period, participants complete a 5-minute cooldown at 10% POmax (watts). An HR monitor wristwatch and transmitter are used to measure HR before exercise and at every minute during warm-up, exercise, and cooldown. Exercise sessions are completed with at least one full day of rest in between each session and are not to be completed on days when the participant has a chemotherapy infusion. Weekly goals will be set by the study staff for each participant based on their symptoms and how they feel overall, allowing for tailored sessions to accommodate individual fitness ability and treatment burden.

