#### AC Group

Participants randomized to this group perform a home-based flexibility intervention 3 days per week for 16 weeks. The stretching protocol consists of the same stretching exercises as in the HIIT program. As flexibility exercises are low-intensity, low-impact, and low-volume, minimal caloric expenditure is expected. To increase compliance [74] and aid in the standardization of the home-based stretching [75], participants are provided with an instructional booklet of the flexibility exercises. Participants are asked to enter these stretching bouts into the daily activity log in addition to the other self-directed exercise sessions performed. Participants in the AC group are offered to participate in the same experimental exercise condition (HIIT) after the first 16-week study period; if they do not choose to participate in the HIIT program, they are not required to complete follow-up testing and are finished with the study after the first 16 weeks. The AC participants who choose to take part in the HIIT protocol after the initial 16 weeks return at the follow-up testing time point for final testing, which serves as post-HIIT testing.

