#### Intervention Adherence

Participant adherence to the HIIT program is measured using (1) percentage and number of prescribed sessions attended (participants must attend ≥80% of the 48 sessions to be considered compliant with the HIIT program; eg, ≥38 sessions) and (2) average minutes of exercise per week (participants must complete ≥80% of the prescribed 90 minutes per week; eg, ≥72 minutes per week). To support adherence throughout the intervention, flexible hours are offered for exercise sessions, including before or after normal working hours and on weekends. In addition, all participants are given an additional 2 weeks beyond the 16-week intervention period to make up for any exercise sessions missed because of illness, work, or travel. Participants are provided with monetary compensation for each MRI completed and parking validation for every visit to the Dana-Farber Cancer Institute.

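### The planned test of adverse events between arms is open to detection bias against HIIT, because the two arms are observed with very different intensity

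*Protocol article*

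**What the plan says.** All references are to the protocol article.

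- **Analysis.** Statistical Analysis states: "Chi-square tests will be used for group comparison of binary outcomes (eg, the occurrence of adverse events"). Effects on binary outcomes are summarized by an odds ratio with a 95% CI, described as the magnitude of the intervention effect. Each analysis is judged at a two-sided .05 level without multiplicity adjustment. The test is not restricted by how or where an event came to light.
- **HIIT arm.** HIIT Group describes clinic sessions "3 days per week for 16 weeks under the supervision of a trained exercise oncology specialist". It adds: "Before beginning the exercise session, participants undergo a screening procedure to ensure that they are fit to participate". The screen covers temperature, heart rate and blood pressure. It also says: "Participants also complete the Therapy-Related Symptom Checklist [73], a 25-item questionnaire, to assess and identify patient-reported symptom occurrence and severity". Intervention Adherence gives the number of sessions: "participants must attend ≥80% of the 48 sessions to be considered compliant with the HIIT program".
- **AC arm.** AC Group states: "Participants randomized to this group perform a home-based flexibility intervention 3 days per week for 16 weeks". For support, "participants are provided with an instructional booklet of the flexibility exercises". Under Physical Activity Logs, the AC daily log records type, duration, intensity and day of exercise. No symptom item is listed.
- **Common to both arms.** Participant Characteristics says that changes in medical conditions, medication and cancer treatment "will be monitored throughout the study period and confirmed at each testing time point". Adverse Events sets one reporting rule for all participants, covering serious and nonserious events until 30 days after the last intervention. It does not describe how events are elicited.
- **Blinding.** Randomization and Blinding states that participants and staff know the allocation once baseline testing is over.

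**The concern.** A comparison of event occurrence between arms measures a treatment effect only if an event has the same chance of being recorded in either arm. Here one arm meets trained staff up to three times a week and is asked about symptoms. For the other arm the article describes no encounter between test visits. These are patients on chemotherapy, so symptoms are expected in both arms whether or not exercise causes any. The arm that is asked more often can be expected to record more of them.

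The likely direction is therefore against HIIT: a spurious excess of adverse events that the plan would report as an intervention effect and could declare significant at .05. This is a pilot meant to inform larger trials, so a false safety signal, or a true one that cannot be told apart from surveillance, would carry forward.

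The same difference in contact bears on the efficacy reading. The comparator is called an attention control, but no staff contact matching the HIIT sessions is described for it. A difference in cognition or self-reported psychosocial health would combine the effect of interval training with that of regular staff contact.

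**Working it through.** **1. The plan's own figure.** 3 sessions per week × 16 weeks = 48 sessions, which agrees with Intervention Adherence. The article gives no adverse event rate and no capture rate, so there is no stated safety figure to reproduce.

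**2. Opportunities for an event to be recorded after baseline, during the intervention.**

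| Route | HIIT | AC |
|---|---|---|
| Test visits (week 9; week 17 or 18) with medical-history confirmation | yes | yes |
| Medical record and common reporting rule | yes | yes |
| Supervised sessions with pre-session screen | up to 48 | none described |
| Therapy-Related Symptom Checklist | yes | none described |
| Ongoing self-report | asked at sessions about outside activity | daily exercise log |

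The first two rows are shared. The next two appear for HIIT only. The last row concerns activity in both arms and does not record symptoms in AC.

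**3. Illustration of size.** The true risks and capture probabilities below are assumptions, because the article supplies neither. The sample is 25 per arm (Sample Size Calculation).

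Let r be the true risk, equal in both arms, and c the probability that an event is recorded. The observed risk is p = r × c. The expected odds ratio is [p1/(1 − p1)] ÷ [p2/(1 − p2)].

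- r = 0.40, c = 0.90 in HIIT and 0.50 in AC: p1 = 0.36, p2 = 0.20; OR = (0.36/0.64)/(0.20/0.80) = 0.5625/0.25 = **2.25**.
- r = 0.30, c = 0.90 in HIIT and 0.60 in AC: p1 = 0.27, p2 = 0.18; OR = (0.27/0.73)/(0.18/0.82) = **1.68**.

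The false-rejection rate is the sum of Bin(i; 25, p1) × Bin(j; 25, p2) over all tables (i, j) for which the uncorrected chi-square test gives P < .05. Tables with no events at all, or with events in everyone, count as no rejection.

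- 36% vs 20%: **25%**.
- 27% vs 18%: **12%**.

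**4. Range.** With capture fixed at 95% in HIIT, 25 per arm, and equal true risks from 20% to 80%:

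| Capture in AC | Expected OR | False rejection |
|---|---|---|
| 95% (equal) | 1.00 | 5% to 6% |
| 75% | 1.33 to 2.11 | 7% to 24% |
| 50% | 2.11 to 4.75 | 15% to 78% |

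With 20 per arm and 50% capture in AC, false rejection is 12% to 64%. With equal capture the test behaves as intended, so the inflation comes from unequal capture and not from the choice of test.

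**The case against.** The strongest reply is that this is a condensed article. Calls to AC participants, the schedule for eliciting adverse events and the content of the case report form may all stand in the full protocol, and their absence here is not a defect. That is right. A reader might infer that AC participants have no contact between test visits, or that the safety comparison is certainly biased. The document supports neither. It shows that the described procedures differ by arm and that the planned test makes no allowance for this.

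Second, some ascertainment is common: both arms attend the same test visits, changes in medical history are followed throughout the study, and one reporting rule covers everyone. This stands as mitigation. It does not equalize the arms, because the test is not limited to events found by those routes.

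Third, the article does not say that checklist answers become adverse events, and completion at every session is implied, not stated. That also stands. The argument does not depend on it: supervision and pre-session screening by unblinded staff already give HIIT more occasions on which an event can be noticed.

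Fourth, the capture rates are invented for illustration. True, and they should not be read as estimates.

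Fifth, adverse event occurrence is not among the listed primary or secondary outcomes, and the pilot aims mainly at effect-size estimation. This limits the stakes, but the comparison is still planned, tested and labelled an intervention effect.

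One might also infer that the chi-square test is wrong for sparse counts. It is not a ground for complaint: at an assumed 10% event rate in both arms and 25 per arm, the same exact enumeration gives a type I error of 4.9%, and the choice of odds ratio or risk difference is a preference.

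**Conclusion.** The concern holds in a limited form. As written, the between-arm test of adverse events is open to detection bias, most likely toward more recorded events in HIIT, because the described opportunities for detection differ by arm and staff are unblinded. The common visits, history checks and reporting rule reduce the imbalance without removing it. The bias is probably smaller for serious events, which are less likely to go unnoticed in either arm.

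Its size cannot be derived from the document. An odds ratio of 2.25 with 25% false rejection follows only if the true risk is 40% in both arms and capture is 90% versus 50%. Milder assumptions give much less, down to 7% false rejection in the range examined.

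On efficacy, the supportable statement is about attribution: no staff contact matching the HIIT sessions is described for AC, so the cognitive and psychosocial contrast is between two packages. It would go too far to say that the randomized comparison is invalid, or that readers are misled about the comparator, which the article openly describes as home stretching. The sample size section is not affected.

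**What to change.** 1. Limit the formal between-arm comparison to (a) events elicited in both arms by the same structured query and the same record review at week 9 and at the postintervention visit, and (b) serious adverse events.
2. Tabulate events detected at HIIT sessions separately and descriptively, without a test or a between-arm odds ratio.
3. State in the interpretation that the cognitive and psychosocial contrast is supervised HIIT with staff contact versus home stretching. If the full protocol provides matched contact or common elicitation for AC, one sentence saying so would answer the corresponding part of this point.

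The cost is a change of analysis wording and one standard query at visits already scheduled. No visits or participants are added. The downside is that fewer events enter the formal comparison, so it will be less precise, and the claim about what caused any cognitive difference becomes more modest. Staff remain unblinded, so fixed wording of the query matters, and some residual bias is possible.

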### Objectives

The primary aim of the Improving Cognitive Function Through High-Intensity Interval Training in Breast Cancer Patients Undergoing Chemotherapy (CLARITY) trial is to examine the impact of a 16-week HIIT exercise intervention on cognitive function assessed using the Montreal Cognitive Assessment, the National Institutes of Health (NIH) toolbox, and quantitative magnetic resonance imaging (MRI) of the brain. We hypothesize that executive function and memory scores will be higher after exercise compared with baseline and the attention control (AC) group and that participants in the HIIT intervention will have enhanced functional brain connectivity and structural white matter tracts compared with baseline and the AC group. The secondary aims are to examine the effects of HIIT on body composition; biomarkers related to metabolic dysregulation, inflammation, and cardiotoxicity; physical fitness and function; and quality of life and psychosocial outcomes in patients diagnosed with early-stage breast cancer undergoing chemotherapy. We hypothesize that participants in the HIIT intervention will have improved body composition and psychosocial health compared with baseline and the AC group.

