##### Physical Activity Logs

The AC group completes a daily activity log throughout the 16-week intervention. During the supervised exercise sessions, the HIIT group is asked about their physical activity completed outside the supervised sessions over the previous week. In addition, they complete daily activity logs during the follow-up period. In the activity logs, the participants are asked to record the type of exercise performed, the time spent performing the exercise, the intensity of the exercise bout (rate of perceived exertion [Borg scale 1-10] or average HR for the HIIT group if they are wearing an HR monitor), and the day of the week in which it was completed.

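### Covariates in the ANCOVA are not confined to values recorded before allocation, and the mixed model leaves the timing of body weight and fat mass open

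*Protocol article*

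**What the plan says.** The Statistical Analysis section describes three between-group analyses of the continuous outcomes:

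- **Two-sample t test** on change from baseline to week 16, unadjusted. Participants moved to MIIT stay in the HIIT arm in the primary analysis.
- **ANCOVA** of the same changes, "adjusting for patient baseline characteristics and other clinical covariates". The sentence goes on to include participants who had to switch to MIIT among these covariates.
- **Linear mixed-effects models**, used both to compare the groups over time and to "explore the impact of potential prognostic factors (eg, body weight, age, fat mass, race, and menopausal status) on outcomes".

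Three sets of data stand under the Covariates heading in Measurements:

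- **Participant Characteristics.** These are taken at baseline, but in addition "Changes in demographic and medical history data (eg, medical conditions, medication, and cancer treatment) will be monitored throughout the study period".
- **Dietary Intake.** Table 1 schedules it at baseline, week 9, the postintervention visit and week 34.
- **Physical Activity Logs.** "The AC group completes a daily activity log throughout the 16-week intervention". HIIT participants are instead asked at supervised sessions about their other activity in the past week, and keep daily logs only in follow-up. Table 1 shows no log before the intervention starts.

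On body composition, the Objectives state: "We hypothesize that participants in the HIIT intervention will have improved body composition and psychosocial health compared with baseline and the AC group". Table 1 schedules anthropometrics at baseline and at every later visit.

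**The concern.** Randomization balances the arms on everything fixed before allocation. A variable recorded afterwards may itself be changed by HIIT, and adjusting for it does two things. It removes whatever part of the effect runs through that variable. If the variable and cognition also share an unmeasured cause, such as how well a patient tolerates chemotherapy, it creates a difference between arms that HIIT did not cause.

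The stated aim of this pilot is to estimate an effect size for a later confirmatory trial. An adjusted estimate that is not the total effect of assignment to HIIT could be carried into that design.

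**Working it through.** **The plan's own figures.** The Sample Size Calculation section says: "We will enroll 50 patients with breast cancer (n=25, 50% per group) in this study"; "Assuming a 20% dropout, data from 40 (n=20, 50% per group) patients will be available for the analyses"; "This sample size offers 80% power to detect a between-group difference at a .05 2-sided *α* level when the difference is 0.91 SD units".

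- Half-width of the 95% CI for a between-group difference: t(0.975, 38) × √(2/20) = 2.024 × 0.316 = 0.640. The plan states 0.64.
- Power at 0.91 SD: noncentrality 0.91 / 0.316 = 2.88. The noncentral t with 38 degrees of freedom gives 0.801. The detectable difference at 80% power is 0.909.

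These figures reproduce. The point concerns model specification and changes none of them; 0.64 SD serves below as a yardstick.

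**Timing of each candidate covariate, from the text.**

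| Variable | Named in a model? | When recorded |
|---|---|---|
| Switch to MIIT | Yes, ANCOVA | After randomization, HIIT arm only |
| Body weight, fat mass | Yes, mixed model | Baseline and later; value to be used not stated |
| Activity logs | No; listed under Covariates | Only after allocation, by a different method in each arm |
| Changes in medication or cancer treatment | No; listed under Covariates | After baseline |
| Diet | No; listed under Covariates | Baseline and later |

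The ANCOVA sets its clinical covariates apart from baseline characteristics, and the one member it names is post-randomization. The category as written is therefore not limited to baseline.

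**Size if on-study values are entered.** The documents give none of the inputs needed, so every input below is an assumption. Variables are scaled to a within-arm SD of 1 in (1).

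1. *Shared cause, true effect zero.* Let HIIT shift outside activity by δ, and let unmeasured tolerance of chemotherapy correlate r₁ with activity and r₂ with cognition. The within-arm slope of cognition on activity is r₁r₂, so the adjusted arm coefficient is 0 − δ·r₁·r₂.
   - δ = −0.5, r₁ = 0.6, r₂ = 0.5: +0.15 SD. With δ = +0.5: −0.15 SD.
   - r₁ = r₂ = 0.4, δ = ∓0.5: ±0.08 SD.
   - A least-squares simulation with 400,000 subjects gave +0.151 / −0.150 and ±0.078. Without the adjustment the bias is zero.

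2. *Mediator, total effect 0.50 SD.* Let HIIT shift a mediator such as fat mass by a, and let the mediator have slope b on the outcome. Adjusting for the on-study value leaves 0.50 − a·b.

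| Shift a | b = −0.2 | b = −0.4 |
|---|---|---|
| 0 | 0.50 | 0.50 |
| −0.25 | 0.45 | 0.40 |
| −0.50 | 0.40 | 0.30 |
| −0.75 | 0.35 | 0.20 |

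   Simulation agreed to within 0.01. Adjusting for the baseline value instead returned 0.492 to 0.504 throughout.

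3. *MIIT indicator, intention-to-treat effect 0.50 SD.* If a proportion p of the HIIT arm switches and switchers do worse by d, the HIIT coefficient compares non-switchers with all controls and equals 0.50 + p·d. For p = 0.1, d = 0.25 it is 0.525; for p = 0.4, d = 0.50 it is 0.70.

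**The case against.** The strongest reply is that the article does not say what a reader might infer, namely that the group comparison will be adjusted for on-study weight, fat mass, activity, diet and treatment changes, so that the adjusted effect certainly fails to be the total effect. Much of this reply stands:

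- Logs, diet and treatment changes are never named as model terms. They appear under a heading in the measurement section, which describes what is collected.
- Weight and fat mass are listed beside age, race and menopausal status and can be read as baseline characteristics. The sentence speaks of exploring their influence on outcomes, not of adjusting the treatment effect for them.
- The t test is unadjusted, so a total-effect estimate is reported whatever the ANCOVA contains. The intention-to-treat statement concerns keeping MIIT participants in the HIIT arm in the primary analysis; it is not claimed for every adjusted model.
- The figure of ±0.15 SD rests wholly on assumed inputs, its sign depends on one of them, and it is small beside the planned half-width of 0.64 SD (0.15 / 0.64 = 23%).

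It can also be said that a condensed article leaves covariate lists and time points to the full protocol or SAP. That is fair for details the article omits. It does not answer what the article states: the ANCOVA opens its covariates beyond baseline and names a post-randomization one. For that model, the reply that baseline is implied fails on the plan's own wording.

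**Conclusion.** The point holds in a limited form. As written, the ANCOVA for the effect of HIIT admits covariates that are not confined to baseline. The Covariates subsection contains data with no pre-allocation value, and the mixed model leaves the timing of weight and fat mass unstated.

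The consequence is conditional. If on-study values are entered, the adjusted coefficient is not the total effect. The bias can go either way and is about 0.08 to 0.15 SD under the shared-cause assumptions. Under the mediator assumptions, a total effect of 0.50 SD would fall to between 0.45 and 0.20 wherever HIIT moves the mediator. The documents support none of these inputs, so they show possible size only. They also do not support concluding that the unadjusted comparison or the sample-size figures are wrong; both are unaffected.

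This is worth correcting because the estimate is meant to inform the next trial and the correction costs almost nothing.

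**What to change.** Add to the Statistical Analysis section:

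- Every covariate in the ANCOVA, and in any mixed model used to estimate the group difference, is a value recorded before allocation. This includes body weight, fat mass, menopausal status and, if used, diet. The rule also takes the MIIT-switch term out of the ANCOVA.
- Activity logs, on-study diet, and changes in medication or cancer treatment are reported by arm and not adjusted for. The report should note that the two arms record activity differently.
- Any model that uses on-study values is labelled exploratory, and no treatment-effect estimate is taken from it.

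If the SAP already contains this rule, the article's ANCOVA sentence should be brought into line with it. The cost is wording only: weight, body composition, diet and participant characteristics are already scheduled at baseline, and no sample-size figure changes.
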